## Abstract

**Background:**

Psychological treatments have been successful in treating chronic low back pain (CLBP). However, the effect sizes are still modest and there is room for improvement. A way to progress is by enhancing treatment adherence and self-management using information and communication technologies (ICTs). Therefore, the objective of this study was to design a trial investigating the short- and long-term efficacy of cognitive behavioural treatment (CBT) for CLBP using or not ICTs. A secondary objective of this trial will be to evaluate the influence of relevant variables on treatment response. Possible barriers in the implementation of CBT with and without ICT will also be investigated.

**Methods:**

A randomised controlled trial with 180 CLBP patients recruited from specialised care will be conducted. Participants will be randomly assigned to three conditions: Control group (CG), CBT, and CBT supported by ICTs (CBT + ICT). Participants belonging to the three conditions will receive a conventional rehabilitation program (back school). The CBT group program will last six sessions. The CBT + ICT group will use the internet and SMS to practice the therapeutic strategies between sessions and in the follow-ups at their homes. Primary outcome variables will be self-reported disability and pain intensity. Assessment will be carried out by blinded assessors in five moments: pre-treatment, post-treatment and 3-, 6-, and 12-month follow-ups. The influence of catastrophizing, fear-avoidance beliefs, anxiety and depression in response to treatment in the primary outcomes will also be analysed.

**Discussion:**

This study will show data of the possible benefits of using ICTs in the improvement of CBT for treating CLBP.

**Trial registration:**

ClinicalTrials.gov, NCT01802671

## Background

Low back pain is a prevalent health condition and a leading cause of disability. It is associated with growing healthcare costs in developed countries, affecting 70% of the general population at some point in their lives, with an annual incidence of 40% [1]. Low back pain presents a tendency to become chronic or produce relapses that can severely impair daily lives of sufferers. In a survey carried out in a Spanish sample, 69% of participants reported low back pain lasting more than three years [2]. Chronic low back pain (CLBP) is the most frequent cause of sick leave and the leading cause of disability in people less than 45 years. The economic burden is approximately 1.7% of the gross domestic product in developed countries and it has been suggested that this problem is even worse in Spain [3]. In this country, CLBP causes 54.8% of days off work [4]. This problem is acquiring epidemic dimensions. In Spain, the number of low back pain episodes has increased from 43,328 in 1993 to 122,995 in 2004, an increase of 183.8% [5].

In 85% of cases, it is not possible to find a precise cause of the pain [1]. The correlation between the symptoms and the MRI findings is very low and there is no relationship between the tendency to chronicity and structural alterations of the spine [6-8]. The patients’ beliefs and attitudes, mainly those related to fear and avoidance, are powerful predictors of CLBP [9-12].

Conservative and interventional medical treatments have a low to moderate effect in CLBP [13]. Empirical evidence suggests that structural changes have a low impact in the treatment of CLBP [7]. Catastrophizing and fear-avoidance beliefs seem to counteract the beneficial effects of conventional and rehabilitation treatment [14,15]. Biopsychosocial perspectives propose taking into consideration structural alterations, as well as psychological and social factors. Although clinical guidelines recommend avoiding rest, promoting activity despite pain and an early return to work, these recommendations have low impact on the improvement of patients. A systematic review about the effect of written information on patients indicated that there was limited evidence of the superiority of a biopsychosocial information brochure compared to a biomedical one on modifying patients’ beliefs about physical activity. Moreover, this approach did not produce changes in pain and disability [16].

Psychological treatments go beyond information about pain. Cognitive behavioural interventions (CBT) address dysfunctional behaviours and beliefs to change behavioural and thinking patterns. These interventions have been successful in treating chronic pain, including CLBP [17]. CBT elicits clinical improvement similar to that achieved with lumbar fusion [18,19]. The COST B13 European guideline [13] recommends CBT in patients with CLBP, especially when surgical interventions are being considered.

Despite the promising results of CBT, it is important to highlight the fact that effect sizes are still modest and that most studies do not include long-term follow-ups. It is necessary to improve CBT programs for CLBP to obtain better therapeutic outcomes and for longer terms. One possible way of improving these programs is by promoting the review of the therapy session contents outside the clinic during the therapy program and once the program is finished. This can be achieved by using information and communication technologies (ICTs) to enhance treatment adherence and self-management.

ICTs have been used already in pain management. There are several studies supporting the efficacy of virtual reality (VR) as a powerful distraction technique for acute pain control associated with medical procedures (see Malloy and Milling, 2010 [20] and Keefe et al., 2012 [21] for a review). There are some preliminary data supporting the use of VR as an adjunct to CBT in fibromyalgia [22] and other medical conditions such as cancer [23]. Another ICT that has been used is the internet; it is now well established in dozens of randomised controlled trials that internet-based therapies are effective in treating several problems [24,25]. Our research group has contributed to this line of research in the field of online therapy for anxiety disorders. In 2000, we developed *“Talk to Me”* and *“Without Fear”*, two internet-based self-applied programs for treating social phobia and small animal phobias [26]. Several case studies and two controlled investigations have shown the efficacy of these programs [27,28]. In the field of chronic pain, there is some evidence of the utility of this ICT in the treatment of several conditions like headache, rheumatoid arthritis, osteoarthritis and fibromyalgia [29-32].

Internet-based interventions are very attractive because they address an important issue in the management of chronic diseases: the possibility of systematic training in self-management strategies. Patients learn and practice therapeutic strategies in their natural environment and on their own, promoting self-management and self-efficacy. In fact, a meta-analysis comparing online and traditional interventions reported a higher increase in knowledge and positive behavioural changes in participants with chronic conditions who had participated in an online program [33].

We have developed an internet-based intervention program called TEO (Terapia Emocional Online) that includes two platforms (therapist and patient platform). The system allows the development and management of different therapeutic contents using multimedia elements (therapeutic information and exercises). Patients and therapists can access these contents online. The aim of this application is to practice the therapeutic strategies outside the consultation room as homework and also during the follow-up periods after the treatment programs have finished.

The objective of this study was to design a randomised controlled trial that investigates the short- and long-term efficacy of a CBT program using ICT or not in CLBP treatment. A secondary objective of this trial will be to evaluate the effect of dysfunctional attitudes and beliefs (catastrophizing and fear-avoidance beliefs), depression and anxiety on treatment response. Possible barriers in the implementation of CBT with and without ICT will also be investigated.

## Methods/design

### Study design

The study will consist of a three-armed (Control, CBT and CBT+ICT) simple-blind randomised controlled trial, with five assessment periods (pre-treatment, post-treatment, and three follow-ups at 3, 6 and 12 months). The study will follow the CONSORT guideline [34].

### Study population

The clinical trial will be conducted in the Valencia-Llíria Health Department in Valencia, Spain. This attends to a population of 320,000 inhabitants. The participants will be referred by medical doctors from the Orthopaedics and Rehabilitation Units. One hundred and eighty participants with a diagnosis of non-specific chronic low back pain according to the definition established by the COST B-13 guideline will be included in the investigation. Patients consecutively referred from primary and specialised care will be invited to participate. Written informed consent will be obtained from all participants. The inclusion criteria are: age between 20 and 65 years; low back pain for at least 6 months; availability of a mobile phone to receive SMS; access to a computer with internet connection to be able to use the CBT program supported by ICT. Exclusion criteria are: mental retardation; not proficient in Spanish; neurogenic claudication or neurologic deficit; history of vertebral fracture; previous lumbar surgery; vertebral infection; spinal or nerve tumour; severe mental disorder; or substance abuse or dependence.

### Randomization

Participants will be randomly assigned to one of three conditions (Control, CBT and CBT +ICT). Participants will be stratified according to their level of disability: severe (Roland Morris Disability Questionnaire (RMDQ) score > 15), moderate (RMDQ score between 8 and 14) and mild (RMDQ score <7). Allocation will be performed by a computer-generated list according to the degree of disability at baseline. It will be supervised by a statistician not belonging to the research group and unaware of the study characteristics.

During recruitment, the allocation sequence will be concealed. Due to the nature of the interventions, it is not possible to blind the participants. The physiotherapists administering the sessions and the assessors will be unaware of the participants’ allocation. Data analysis will be conducted without being aware of the intervention received by the participants.

### Sample size

The study has been designed taking into consideration changes of 2 points in the pain intensity measured by the numerical rating scale (NRS) and of 3 points in the RMDS. These changes have been recognised as clinically relevant [35]. According to the results of a previous CLBP sample treated in our health centre, the mean disability according to the RMDS presented a standard deviation of 4, while the mean pain intensity displayed a standard deviation of 2. Considering these data and an alpha of 0.01 and a beta of 0.9 for two-tailed mean tests, the required sample size is 53 to detect changes in disability and 30 to detect changes in pain intensity. Considering an attrition of 15%, the sample will need 60 participants per condition. For further analysis of treatment response according to high or low catastrophizing, fear-avoidance beliefs, depression and anxiety, disability measured by the RMDS will be considered with an alpha of 0.05 and beta of 0.8, resulting in a sample size of 28 participants per group.

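### Sixty per arm does not cover 15% attrition from 53 (63 would), so disability power is about 89% rather than 90%, and power is mislabelled as beta

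*Protocol article*

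**What the plan says.** The Sample size section of the protocol article plans for "changes of 2 points in the pain intensity measured by the numerical rating scale (NRS) and of 3 points in the RMDS". It takes the variability from an earlier sample at the same centre: "the mean disability according to the RMDS presented a standard deviation of 4", and "the mean pain intensity displayed a standard deviation of 2". It then gives the error rates and the first result: "an alpha of 0.01 and a beta of 0.9 for two-tailed mean tests, the required sample size is 53 to detect changes in disability", with 30 as the corresponding figure for pain. The next sentence makes the attrition allowance: "Considering an attrition of 15%, the sample will need 60 participants per condition".

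Three arms of 60 give the total that appears in the Abstract, "A randomised controlled trial with 180 CLBP patients recruited from specialised care will be conducted", and again under Study population. The Sample size section closes with a calculation for the analysis of treatment response by psychological characteristics. It uses alpha 0.05 and a value of 0.8 that is again called beta, and arrives at 28 per group.

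**The concern.** Two things in the Sample size section do not fit together.

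- **Attrition.** If 15% of 60 are lost, 51 remain. The sentence before says that 53 are needed. The allowance therefore fails to protect the number it was meant to protect, and the total of 180 inherits the slip. The attrition-adjusted number is the relevant one, because Collection and data analysis places the primary analysis at month 12, the last of the five assessments.
- **Terminology.** Beta is the type II error rate. A beta of 0.9 is not a design anyone would choose, and the same usage recurs with 0.8.

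At stake is whether the power stated for disability, the primary outcome that drives the sample size, agrees with the enrolment and attrition written beside it.

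**Working it through.** **Inputs, all from the Sample size section:** difference 3 points and SD 4 (disability); difference 2 points and SD 2 (pain); two-sided alpha 0.01; intended power 0.90; attrition 15%; 60 per condition. The 53 and 30 are read as per-arm figures, because the 60 derived from them is per condition.

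**1. Reproduce the base figures.** Normal approximation for two means, equal allocation:

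n per arm = 2 × (z for alpha + z for power)² × SD² / difference²

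- Disability: 2 × (2.576 + 1.282)² × 16/9 = 52.9, so 53. Matches.
- Pain: 2 × (2.576 + 1.282)² × 4/4 = 29.8, so 30. Matches.
- Treatment-response calculation (alpha 0.05, power 0.80, difference 3, SD 4): 28. Matches.

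**2. Test the beta label.** If 0.9 really were beta, power would be 0.10, and the same formula would give 6 (disability) and 4 (pain). The printed 53 and 30 therefore rest on power 0.90, and the printed 28 on power 0.80.

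**3. Attrition step.**

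- Inflation that preserves 53 completers: 53 / (1 − 0.15) = 62.35, so 63 per arm and 3 × 63 = 189 in total.
- The common shortcut: 53 × 1.15 = 60.95, which is 61 when rounded up. Only truncation gives 60.
- Reverse check: 60 × 0.85 = 51 completers, 2 below 53.
- Loss that 60 can absorb: 60 − 53 = 7 participants, and 7/60 = 11.7%.
- Shortfall in enrolment: 63 − 60 = 3 per arm, or 9 in total (9/180 = 5%).

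**4. Effect on power, same method as the 53.** Power = Φ(difference / (SD × √(2/n)) − 2.576):

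| Outcome | Completers per arm | Power |
|---|---|---|
| Disability | 53 | 90.1% |
| Disability | 51 | 88.7% |
| Pain | 51 | 99.3% |

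For disability at 51: 3 / (4 × √(2/51)) = 3.787; 3.787 − 2.576 = 1.211; Φ(1.211) = 0.887. The shortfall from 90% is about 1.3 points.

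**5. Cross-check with the noncentral t distribution.** Disability power is 88.9% at 53 and 87.5% at 51. The attrition slip costs about 1.4 points on this scale too. The remaining 1.1 points below 90% (90 − 88.9) come from the change of formula and are present even at the protocol's own 53.

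**The case against.** The strongest reply is that neither slip matters in practice, and much of it stands.

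- **The label changes no number.** A reader might infer from the wording that the trial was planned with 10% power, or 20% for the treatment-response analysis. The document rules this out, because its own 53, 30 and 28 arise only with power 0.90, 0.90 and 0.80.
- **The loss is about one point.** A reader might also infer that the trial fails to deliver its stated power in any material sense. It does not: disability stays near 89%, and pain is far above 90%.
- **A figure of about 87% would be unfair.** It comes from the t distribution, on which 53 per arm would not reach 90% either. Setting it beside a 53 obtained by normal approximation charges attrition with a difference in method.
- **The planned analysis may recover the loss.** Collection and data analysis specifies ANCOVA with the baseline value as covariate, whereas the calculation is for an unadjusted comparison of means. The protocol gives no baseline correlation. As an assumption, take SD 4 as the unadjusted follow-up SD. The effective SD is then 4 × √(1 − r²), and power at 51 per arm runs from about 90% (r = 0.2) to about 96% (r = 0.5).
- **Group delivery of CBT does not enlarge this point.** One might want to add a clustering penalty, but the document gives no intracluster correlation, so no size can be attached here.

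What the reply does not remove is the contradiction itself. The section states a requirement of 53, assumes 15% loss, and names a number that leaves 51. It claims no gain from covariate adjustment that would bridge the gap.

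**Conclusion.** The point holds as a minor correction. Inflating 53 for 15% attrition gives 63 per arm (189 in total), not 60 (180). With 60 per arm and the stated attrition, 51 completers are expected, and the unadjusted comparison of disability has about 88.7% power instead of 90%. Pain is unaffected in substance, at about 99%. Writing beta for power is an error of terminology with no numerical effect.

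The conclusion rests on reading 53 as a per-arm figure, on the protocol's differences, SDs and two-sided alpha of 0.01, and on the normal approximation that reproduces its figures. It does not show that the trial is underpowered to a degree that matters. For the baseline-adjusted analysis a shortfall is not established, since a modest baseline correlation would offset it.

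**What to change.** Keep 60 per arm and 180 in total, and correct the statement in the Sample size section in one of two ways, both on the protocol's own method:

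- With 60 randomised per arm and 15% attrition, 51 completers are expected, giving about 89% power at two-sided alpha 0.01 for a 3-point difference in disability (SD 4); or
- With 60 randomised per arm, 90% power for disability holds for up to 7 losses per arm (11.7% attrition).

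In the same section, change the two beta values to power 0.9 (beta 0.1) and power 0.8 (beta 0.2). The figures 53, 30 and 28 stay as they are.

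The cost is a few words. Enrolment and analysis do not change, and the totals in the Abstract and under Study population can stand. The only price is a stated power about one point lower, or a stated attrition allowance about three points lower (15% to 11.7%).

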Intra-group changes in the continuous variables along the time points will be explored with Student’s T-test for paired samples. To assess if there are differences among the groups according to pain, disability and the rest of the variables, we will use analysis of covariance (ANCOVA) for each dependent variable. In all the tests, the independent variable will be the group, while the covariate variable will be the basal level of each dependent variable. It will be necessary to have comparable levels of both types of variables to understand correctly the ANCOVA results. Therefore, we will perform different Student’s T test estimations, one for each dependent variable, considering each group as an independent variable in each case. To evaluate whether the changes in the three groups have happened in a different way, we will estimate different ANOVA, an analysis for each dependent variable. In all cases, the independent variable will be the group and time in which the data are collected. In this analysis, we will also study possible interactions. Furthermore, we will evaluate the correlations between the variables using Rho-Pearson and Spearman according to normality. We will also use two multiple linear regression models for pain and disability as dependent variables and in both models, gender, age, pain, catastrophizing, fear avoidance, days taken off at work and time evolution will be employed as independent variables.

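### The secondary treatment-response analysis is sized on high/low splits of four scores, has no matching model in the analysis section, and would keep more power with the scores left continuous

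*Protocol article*

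**What the plan says.** The Abstract and the Background of the protocol article make the influence of catastrophizing, fear-avoidance beliefs, anxiety and depression on response to treatment a secondary objective.

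The Sample size section turns this into a comparison of groups: "For further analysis of treatment response according to high or low catastrophizing, fear-avoidance beliefs, depression and anxiety". The outcome for this calculation is disability on the Roland-Morris scale, with "an alpha of 0.05 and beta of 0.8, resulting in a sample size of 28 participants per group".

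The Secondary outcomes section describes the instruments (HADS, FABQ, PCS) as scores and gives no threshold for high or low.

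The Collection and data analysis section contains no high/low comparison. The factors appear only in "two multiple linear regression models for pain and disability as dependent variables", where "gender, age, pain, catastrophizing, fear avoidance, days taken off at work and time evolution will be employed as independent variables". Catastrophizing and fear avoidance are in that list; anxiety, depression and treatment arm are not. The only interactions mentioned belong to an ANOVA whose factors are group and time.

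**The concern.** There are two linked problems.

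First, the analysis that was sized is not an analysis that is described. Read literally, the regressions ask which variables go with pain or disability. Without an arm term and an arm-by-factor term they cannot show whether the benefit of CBT, with or without ICT, depends on a patient's catastrophizing, fear avoidance, anxiety or depression. Nothing in the section covers anxiety and depression in this role at all.

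Second, the one form that the article does commit to is a two-group split of a graded score. Patients just either side of the cut are treated as different, and all patients on one side as alike. Questions about differential response are already short of power in a trial sized for main effects, and a split spends part of what is available. What is at stake is a named secondary objective, not the primary comparison.

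**Working it through.** **Inputs from the Sample size section.** Difference: "of 3 points in the RMDS". Spread: "the mean disability according to the RMDS presented a standard deviation of 4". Arm size: "Considering an attrition of 15%, the sample will need 60 participants per condition", which leaves 60 × 0.85 = 51 completers. The main calculation is two-tailed, and I assume that this carries over. The stated beta of 0.8 is read as power 0.80, the reading that reproduces the plan's figure.

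**1. The plan's own figure.** For a comparison of two means, n per group = 2 × [SD × (z₀.₉₇₅ + z₀.₈₀) / difference]² = 2 × [4 × (1.960 + 0.842) / 3]² = 27.9, so 28. It reproduces. It is the size for a simple two-group difference of 3 points, not for a difference in treatment effect between high and low patients.

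**2. What the 28 implies.** If arms are compared within a high or low stratum, the cell sizes depend on the cut:

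| Cut | Smaller cell, 60 per arm | Power | Smaller cell, 51 per arm | Power |
|---|---|---|---|---|
| 50/50 | 30 | 0.83 | 25.5 | 0.76 |
| 70/30 | 18 | 0.61 | 15.3 | 0.55 |

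So 28 per cell is available only with a cut near the median and before attrition. If the target is a 3-point difference in treatment effect between high and low, the standard error with 28 per cell is 4 × √(4/28) = 1.51 and power is about 0.51. About 4 × [4 × 2.802 / 3]² = 56 per cell would be needed.

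**3. Information kept by a split.** For a normal score cut at quantile p, the share kept is φ(z_p)² / [p(1 − p)].

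| Cut | Kept | Lost |
|---|---|---|
| 50/50 | 2/π = 63.7% | 36.3% |
| 60/40 | 62.2% | 37.8% |
| 70/30 | 57.6% | 42.4% |
| 75/25 | 53.9% | 46.1% |
| 80/20 | 49.0% | 51.0% |

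Under normality the median is the most favourable of these cuts.

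**4. Illustration in power.** Take one pair of arms, 51 completers each, residual SD 4, two-sided alpha 0.05. Assume a linear interaction that makes the two halves differ by 3 points in treatment effect. The halves of a normal score have means 2 × √(2/π) = 1.596 SD apart, so the slope is 3 / 1.596 = 1.88 points per SD.

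- Continuous score: SE = 4 × √(2/51) = 0.79, z = 1.88 / 0.79 = 2.37.
- Median split: SE = 4 × √(4/25.5) = 1.58, z = 3 / 1.58 = 1.89.
- Ratio of the squared z values: (1.89 / 2.37)² = 0.64, in agreement with 2/π.

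A simulation of 20,000 runs (least squares with arm, factor and interaction) gave power 0.633 for the continuous score and 0.444 for the median split, a gap of 19 percentage points.

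The levels move with the assumed effect and the gap changes little. With a larger slope of 2.22 points per SD, a simulation of 4,000 runs at 51 per arm gave about 0.77 and 0.57.

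**The case against.** The strongest reply has four parts.

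- **A contradiction is not shown.** A reader might infer that the article defines the same factors in two incompatible ways, as groups in one section and as slopes in another. The text does not support that. The regression list covers two of the four factors, never says whether they enter as scores or categories, and has no treatment term, so it may be a separate predictor analysis. This stands. What remains is a sized analysis with no described counterpart.
- **The cut may be fixed elsewhere.** A reader might infer that the cut would be chosen after the data are seen. Nothing in the article says so. A full protocol or analysis plan could hold a clinical threshold. This also stands, and the absence of a cut is not in itself the point. The cut matters here only because the 28 per group and the size of the loss depend on it.
- **Subgroups are a legitimate, readable choice.** They do not need linearity, and if response really changes at a threshold, a split there need not lose power. This stands in part: the advantage of the continuous score rests on the effect being roughly linear. Readability can be kept by showing fitted effects at chosen score values.
- **The figures rest on assumptions.** They do, and they are given as a range and an illustration. A reader might also infer that the two forms would give opposite conclusions. The calculation shows a difference in power, nothing more.

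**Conclusion.** The point holds as an improvement to a secondary analysis. The Sample size section commits to a high/low analysis of four scores, and the Collection and data analysis section offers no model for it and no model for differential response to treatment. The two sections have to be reconciled, and a continuous score is the better form in which to do so.

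The loss from splitting is about 36% of the information at a median cut and about 51% at 80/20, given a normal score and a linear effect. It would be wrong to say that the plan discards about a third of the information without those conditions, because the article states neither the cut nor the distribution. The 63% against 44% power further assumes one pair of arms, 51 completers each, the article's SD of 4 as residual SD, and a 3-point difference in treatment effect between halves. The article does not state that last target; its 3 points is a clinically relevant change in disability.

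The 60 per condition and the primary ANCOVA are untouched.

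**What to change.** In the Sample size section, replace the high/low wording with each factor's continuous baseline score: PCS total, the FABQ subscales, HADS anxiety and HADS depression. The 28 per group then no longer describes the analysis. It can give way to a statement of what the trial can detect: with 51 completers per arm and SD 4, 80% power corresponds to a slope difference of about (1.960 + 0.842) × 4 × √(2/51) = 2.22 points per SD of the score by the normal approximation (simulated power about 0.77).

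In the Collection and data analysis section, add a baseline-adjusted model for disability and one for pain, for each score, with arm, score and arm-by-score interaction. The interaction is the test of differential response. Show fitted treatment effects at, for example, the 25th and 75th percentiles. State whether the existing regressions are a separate predictor analysis and how their variables are coded. Keep high/low groups for description only.

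The cost is wording: the scores are collected in any case. The small downside is a linearity assumption, which a curvature term can check.

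### The 28 per group for response by high or low moderator sizes a simple two-mean comparison; a 3-point difference in treatment effect between strata needs about 56 per arm per stratum

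*Protocol article*

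**What the plan says.** The main calculation in the Sample size section uses a change "of 3 points in the RMDS" and a previous sample in which "the mean disability according to the RMDS presented a standard deviation of 4", with "an alpha of 0.01 and a beta of 0.9 for two-tailed mean tests". It ends with "Considering an attrition of 15%, the sample will need 60 participants per condition".

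A second calculation, again on Roland-Morris disability, is stated "with an alpha of 0.05 and beta of 0.8, resulting in a sample size of 28 participants per group". The article gives its purpose in these words: "For further analysis of treatment response according to high or low catastrophizing, fear-avoidance beliefs, depression and anxiety". No effect size or SD is restated for it, no attrition allowance is attached to it, and group is not defined.

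The Abstract and the last paragraph of the Background make the influence of these variables on the response to treatment a secondary objective. Collection and data analysis plans group-by-time ANOVAs with interactions. It also plans two linear regressions that list catastrophizing and fear avoidance among the predictors. Neither treatment arm nor an arm-by-moderator term appears in that list.

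**The concern.** Whether patients high and low on a moderator respond differently to treatment is a contrast of two treatment effects. It carries the sampling error of four cells, whereas a formula for comparing two means carries that of two. A size taken from the two-mean formula will be too small for it unless the interaction is assumed to be larger than the main effect, and the article does not assume that. The stated attrition may also take the cells below 28.

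At stake is how the secondary objective can be read. The article presents it as sized at 80% power. If power is well below that, a null moderator result says little about whether high and low patients benefit equally, and a reader who trusts the stated power could give it too much weight. The primary comparison is not affected.

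**Working it through.** **Inputs from the Sample size section:** difference 3 points, SD 4, alpha 0.05, 60 per arm, attrition 15%. Two-sided testing is stated for the main calculation and carried over. The printed beta of 0.8 is read as power 0.80, the reading that gives 28. **Assumptions of this check:** an even high/low split unless stated otherwise, and a 3-point interaction, because the article gives no cut-point and no interaction size.

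**1. The plan's own figure.** n = 2(1.960 + 0.842)² × 4² / 3² = 27.9, so 28 per group. It reproduces exactly. A one-sided test would give 22.

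**2. Cell size available.** 60 × 0.85 = 51 completers per arm; 51 / 2 = 25.5 per arm per stratum. As enrolled, 60 / 2 = 30, which covers 28; after attrition it does not. Keeping 28 per cell would need 56 / 0.85 = 65.9, so 66 per arm.

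**3. Simple 3-point effect within one stratum.** SE = 4√(2/25.5) = 1.120; power = Φ(3/1.120 − 1.960) = 76% (75% with the t distribution). In the smaller cell of a 30/70 split (15.3 per arm), SE = 4√(2/15.3) = 1.446 and power is 55%.

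**4. Difference in effect between strata, two arms.** SE = 4√(4/25.5) = 1.584; power = Φ(3/1.584 − 1.960) = 47% (also 47% with the t distribution). Detectable at 80% power: (1.960 + 0.842) × 1.584 = 4.4 points. Size for 80% power at 3 points: 4(1.960 + 0.842)² × 4² / 3² = 55.8, so 56 per cell. That is 112 completers per arm, 132 enrolled per arm (112 / 0.85 = 131.8), and 396 in three arms. With a full 28 per cell, power would still be only 51%.

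**5. Sensitivity of the 3-point interaction.** Baseline adjustment replaces SD 4 by 4√(1 − r²).

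| Assumption | SE | Power |
|---|---|---|
| Even split, unadjusted | 1.584 | 47% |
| 40/60 split | 1.617 | 46% |
| 30/70 split | 1.729 | 41% |
| 25/75 split | 1.829 | 37% |
| Both CBT arms pooled against control, even split | 1.372 | 59% |
| Baseline correlation 0.3, even split | 1.511 | 51% |
| Baseline correlation 0.5, even split | 1.372 | 59% |
| Baseline correlation 0.7, even split | 1.131 | 76% |

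On the first row's basis, interactions of 2, 4 and 6 points have 24%, 71% and 97% power.

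**6. The other reading of group.** High against low among all CBT-treated completers is about 51 against 51 (102 completers in two arms). SE = 4√(2/51) = 0.792 and power for 3 points is 97%.

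**The case against.** The strongest reply is that 28 contains no arithmetic error and that the interaction is the reviewer's quantity. The article never states an interaction size. Its 3 points are a clinically relevant change, not a difference between two effects. The planned regressions use the moderators as predictors, which fits a comparison of high with low among treated patients, and on that reading 28 is comfortably exceeded. The main analysis is an ANCOVA on baseline, so unadjusted power is probably pessimistic. With an assumed correlation of 0.3 even the within-stratum comparison at 25.5 per cell is back at 80%. Cut-points and model form are matters a condensed article may leave to the full plan.

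Much of this stands. A reader might infer that the true power is 47% rather than 80%. The documents do not support that, because 47% depends on a 3-point interaction, an even split, SD 4 without adjustment and one pairwise arm contrast. A reader might also blame attrition for the loss. Attrition alone takes power only from 80% to about 76%, and nearly all of the rest comes from moving to the interaction. The missing cut-point is not a fault here, and the case against splitting continuous scores is secondary.

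What does not stand is the rescue by pooling. Comparing high with low among treated patients, with no control contrast, shows prognosis. It cannot show that treatment works differently in the two strata, which is the stated objective. The article chose to print a size and power for this analysis, so whether that size fits the objective is a fair question.

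**Conclusion.** The point holds in a limited form. The 28 per group is correct for a simple two-mean comparison and does not size the moderator objective: a 3-point difference in treatment effect needs 56 per arm per stratum, twice the stated figure. If group means arm within stratum, the design's own attrition leaves 25.5 per cell on an even split, below 28, with about 76% unadjusted power for a simple effect and less in the smaller cell of an uneven split.

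Power for a 3-point interaction is about 47% on the plain inputs and stays below 80% in every 3-point scenario examined (37% to 76%). It would pass 80% only for a larger interaction, about 4.4 points or more unadjusted, or with stronger baseline adjustment than assumed here. The 80% claim is therefore unsupported for differential response. No single replacement figure can be called the true power.

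**What to change.** In the Sample size section:

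- Withdraw the 80% claim for the moderator objective and define group.
- State either the power for a named interaction or the interaction detectable at 80% power, with the split, SD, baseline adjustment and arm contrast it assumes. On the unadjusted even-split basis these are about 47% for 3 points, or 4.4 points detectable.
- If 28 is kept, say that it refers to a simple comparison, say which one, and allow for attrition.

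In Collection and data analysis:

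- Test moderation with arm-by-moderator terms, preferably using continuous PCS, FABQ and HADS scores, with high/low groups kept for display.
- Label the analysis exploratory and report interaction estimates with confidence intervals, so that a null result is not read as equal response.

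The cost is wording and model specification. The stated power becomes less favourable. No extra patients are needed, and the 60 per arm does not rest on this figure.
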